### Experimental (RISE intervention + usual care) group

Participants in the experimental group receive usual care, according to national guideline ‘diagnostics, treatment and care for participants with a stroke’ and the RISE intervention.^18^

The RISE intervention is based on the behaviour change wheel (BCW), a method guiding the development of behaviour change interventions.^19^ Extensive explanation on the development of the RISE intervention and the (co-)design process can be found elsewhere.^13^ Preliminary effectiveness and feasibility of the RISE intervention have been determined in a randomised multiple baseline study.^14^ After the pilot study, minor refinements have been implemented in the current study: an updated version of the RISE device is used and the user interface of the RISE app was updated based on participants’ input.

The RISE intervention is a 15-week blended behavioural intervention, in which a trained primary care physiotherapist coaches participants to reduce and interrupt their sedentary time (figure 2). Physiotherapists provide personalised coaching to people with a stroke in their home setting by using behaviour change techniques and the *RISE eCoaching system* (table 2). The RISE eCoaching system consists of: (1) an activity monitor, (2) a smartphone application that provides real-time feedback and contains e-learning modules and (3) a monitoring dashboard for the physiotherapist. The e-learnings consist of weekly videos about self-management provided with assignments and text. Topics are: lifestyle factors, movement behaviour including SB, examples of reducing SB, participant expectations, action planning, coping planning, PS, a set-back and prevention plan. The intervention is protocolised per week (table 2) and personalised for each participant’s goals, action plans, coping strategies and setbacks. The RISE eCoaching system provides insights into 24-hour movement behaviour and facilitates goal setting and personalised feedback. It recommends goals based on past movement behaviour and graded activity principles, which the physiotherapist and participant finalise together, appearing in the RISE app.^20^ Participants monitor their progress and receive tailored feedback based on their actual movement behaviour compared with their goals (figure 2). Physiotherapists also offer sleep improvement tips if needed.

**Figure 2 F2:**
[figure not shown]
RISE eCoaching system consists of: (1) an activity monitor, (2) a smartphone application that provides real-time feedback and contains e-learning modules and (3) a monitoring dashboard for the physiotherapist.

**Table 2 T2:** Overview protocol RISE intervention

Week	Mode of delivery	Main topic	Elements	Behaviour change techniques^21^
1	At participants’ home (meeting 1)	Introduction of the intervention	Intake Information about the intervention and the purpose and importance of healthy movement behaviour Start self-monitoring	Information about health consequences
	eCoaching	Benefits of reducing sedentary behaviour (1)		Information about health consequences
2	At participants’ home (meeting 2)	Behavioural diagnosis	Coaching sessions to identify facilitators and barriers Discussing the movement behaviour	Goal-settingFeedback on behaviourGraded taskNon-specific reward
	eCoaching	Benefits of reducing sedentary behaviour (2)		Information about health consequences
3	At participants’ home (meeting 3)	Self-monitoring	Discussing movement behaviour Discussing own beliefs about reducing sedentary behaviour Discussing possible barriers Setting cues	Goal-settingFeedback on behaviourHabit reversalReview behavioural goalsBehaviour substitutionPrompts and cuesProblem-solving
	eCoaching	What is self-monitoring?		Feedback on behaviour
4	At participants’ home/online/at physiotherapy practice (meeting 4)	Action planning and goal-settingSleep check	Goal-setting and monitoring Self-monitoring Discussing sleep hygiene rules Developing a strategy to sit less	Goal-settingFeedback on behaviourHabit formationDemonstration of the behaviourInstructions on how to perform the behaviour
	eCoaching	Prompts and cues		Prompts and cues
5	At participants’ home/online/at physiotherapy practice (meeting 5)	Building social support	Discussing the movement behaviour Creating an action plan Discussing the possibilities for social support	Action planningGraded tasksSocial support (unspecified)Social support practicalReview behavioural goals
	eCoaching	Maintenance task self-efficacy		Habit formation
6	At participants’ home/online/at physiotherapy practice (meeting 6)	Increasing self-confidence for reducing sedentary behaviour	Reviewing movement behaviour of past week Providing positive feedback Discussing successes Discussing action plan Discussing social environment Reducing cues	Action planningFeedback on behaviourSocial support (unspecified)Social support practicalGraded task
7	eCoaching	Review own behaviour and the social and physical environment		Review behavioural goals
8	At participants’ home/online/at physiotherapy practice (meeting 7)	Introduction of setbacks	Discussing past week Reinforcing successes Discussing action plan Making an action plan to rearrange physical environment	Feedback on behaviourAction planningRestructuring the physical environmentFocussing on past successes
9	eCoaching	Habit formation and coping planning		Habit formation
10	At participants’ home/online/at physiotherapy practice (meeting 8)	Habit formation and setbacks	Reflection on process so far Feedback on behaviour by participant Reflecting on previous action plan Discussing habits and setbacks Setting a challenging goal and action plan	Feedback on behaviourAction planningFocussing on past successesHabit formation
11	eCoaching	Sustainable change		Behaviour substitution
12	At participants’ home/online/at physiotherapy practice (meeting 9)	Self-monitoring	Discussing past weeks Discussing action plan Discussing pros and cons of reducing sedentary time Discussing activity monitor for after the intervention period Discuss sleep hygiene rules	Feedback on behaviour Action planningReview behavioural goalsGraded task
13–14	eCoaching	Specific action and coping plan for the futureSleep		Discrepancy between current behaviour and goal
15	At participants’ home/online/at physiotherapy practice (meeting 10)	Future proof	Review movement behaviour Addressing remaining questions Action plan for future Closing	Review behavioural goalsAction planningCommitmentBehaviour substitutionValued self-identityFocus on success

Participants will receive *PS* from someone from their social network (eg, a partner or close friend) who joins them in the intervention. The PS will attend all RISE sessions and will use their own RISE eCoaching system. Our pilot study showed that the group with PS had a greater reduction in sedentary time than the group without PS.^14^

The intervention will be delivered by ±130 primary care *RISE physiotherapists* specialised in neurological care. All physiotherapists will be extensively trained in four sessions of 3–4 hours focused on behaviour change techniques, the RISE protocol and motivational interviewing. The training is accredited by the Royal Dutch Society for Physiotherapy. After the training, physiotherapists will join an online learning community, where RISE-related questions or cases will be shared during 3-monthly booster sessions. Physiotherapists make use of the following behaviour change techniques: goal-setting (on behaviour and outcome), action planning, social support, self-monitoring of behaviour, feedback on behaviour, discrepancy between current behaviour and goals, information about health consequences, problem-solving, restructuring the social environment, prompts and cues, habits formation and instructions how to perform the behaviour^21^ (table 2).

### Control group (usual care)

There will be no restrictions for receiving other care as usual. Participants in the experimental and control group receive usual care according to national stroke guidelines.^18^ At T1–T4, participants are asked about all of their healthcare utilisation via the institute for Medical Technology Assessment (iMTA) Medical Consumption Questionnaire (iMCQ) (^22^).

### Outcome measurements

An overview of all the outcome measurements obtained and the accompanying time points is given in table 3. A timeline for the follow-up measurements is provided in figure 1.

**Table 3 T3:** Summary of outcome measurements

	Parameter	Measurement instrument	T0	T1*4 months*	T2*6 months*	T3*9 months*	T4*12 months*
Primary	Major adverse cardiovascular event	Medical records from GP		X	X	X	X
Secondary	Healthcare utilisation	iMTA Medical Consumption questionnaire^22^		X	X	X	X
	(Unpaid) productivity losses	iMTA Productivity Cost questionnaire^22^		X	X	X	X
	Quality of life	Euro Quality of Life 5 Dimensions^26^	X	X	X	X	X
	24-hour: sedentary behaviour	ActivPAL^59^	X	X	X		X
	24-hour: physical activity	ActivPAL	X	X	X		X
	24-hour: sleep	Emfit QS sleep tracker^31^	X	X	X		X
Tertiary	Physical functioning	Short Performance Physical Battery^30^	X	X			
	Sleep quality	Pittsburgh Sleep Quality Index^32^	X	X	X		X
	Level of fatigue	Fatigue Severity Scale-7^33^ and Visual Analogue Scale^33^	X	X	X		X
	End-user satisfaction*	End-User Computing Satisfaction^35^	X	X			
	Feasibility*	Post-Study System Usability Scale^36^		X			
	Acceptability*	System Usability Scale^37^		X			
	Compliance†	Compliance questionnaire		X			
	Self-efficacy	Self-Efficacy for Symptom Management Scale^34^	X	X	X		X
	Self-management skills	Patient Activation Measure^28^	X	X	X		X
Other	Stroke impact	Stroke Impact Scale – Physical^38^	X	X	X		X
	Mental health	Hospital Anxiety and Depression Scale^39^	X	X	X		X
	Comorbidities	Cumulative Illness Rating Scale^40^	X				
	Body Mass Index	Centimetre and scale	X	X			
	Walking speed	5 Metre Walking Test^41^	X	X			
	Blood pressure	Blood pressure monitor	X	X			
	Cognitive functioning	Montreal Cognitive Assessment^60^	X				
	Patient characteristics‡	Intake questionnaire	X				
	Stroke characteristics§	Intake questionnaire	X				
	Vascular risk factors¶	Intake questionnaire	X				
	Stroke severity	National Institutes of Health Stroke Scale^42^	X				

T0=baseline measurement, within 6 months post stroke, T1=four months post randomisation, T2=six months post randomisation, T3=nine months post randomisation, T4=one year post randomisation.

* In participants in the experimental group and physiotherapists.

† In physiotherapists and participants in the experimental group.

‡ Patient characteristics: age, gender, education level, living situation (number of persons in the household).

§ Stroke characteristics: type of stroke, side of stroke, time since stroke.

¶ Vascular risk factors: coronary artery disease, atrial fibrillation, diabetes, hypertension, clinical obesity, smoking and alcohol use, hyperlipidaemia.

GP, general practitioner.

### Primary outcome

The effect of the RISE intervention on the number of MACE will be measured based on the 2000 Consensus Conference of the European College of Cardiology and American College of Cardiology criteria.^23^ MACE is a composite of clinical end points of recurrent stroke or TIA, acute coronary events and cardiovascular death.^3^ Stroke recurrence will be diagnosed by acute neurological symptoms and signs and confirmed by MRI. TIAs are defined according to American Heart Association guidelines.^24^ Acute coronary events (myocardial infarction (MI), cardiac revascularisation and hospitalisation with unstable angina) are diagnosed according to the 2000 Consensus Conference of the European College of Cardiology and American College of Cardiology criteria.^23^ Deaths are regarded to be attributable to a cardiovascular cause (fatal MI, fatal stroke (ie, death within 1 month of MI or stroke), sudden death caused by definite coronary artery disease and congestive heart failure) unless a non-cardiac death could be confirmed. Recurrence of MACE will be collected via medical records of the GP. In the Netherlands, where this study takes place, all hospital-based care—including diagnoses, admissions and clinical events—is systematically reported back to the participants’ GP. Additionally, participants are asked in a questionnaire if any MACE occurred. In case of any discrepancy between the GP’s medical record and questionnaire, the researchers will contact the GP to obtain the correct information from the medical professionals involved. Data from the GP’s medical record will remain the primary source of data collection.

### Secondary outcomes

Cost-effectiveness of the RISE intervention will be assessed for MACE prevention and QALYs. QALYs will be based on the participants’ responses to the Euro Quality of Life 5 Dimensions.^25^ These responses will be converted into utility values using the Dutch tariff, after which QALYs will be estimated using linear interpolation between measurement points.^26^ All costs related to the RISE intervention will be considered: that is, costs of the intervention, other healthcare utilisation, informal care, sports equipment and memberships, as well as losses from unpaid and paid work (ie, absenteeism and presenteeism). Intervention costs will be microcosted, meaning that detailed data will be gathered about the number and kinds of resources that are used while providing the RISE intervention, as well as information about their respective unit costs. All other kinds of resource use will be measured at T1–T4, using modified versions of the iMCQ and the iMTA Productivity Cost Questionnaire.^27^ Resource use will be valued in accordance with the Dutch manual for costing studies in healthcare.^22^

Change in 24-hour movement behaviour will be measured in the experimental and control group. The 24-hour (SB, physical activity and sleep) is measured with the ActivPAL (PAL Technologies Ltd, Glasgow, UK).^28^ This monitor is a combination of a triaxial accelerometer and inclinometer, worn on the anterior side of the unaffected thigh and detects if someone is either sedentary (sitting, lying or reclining), standing or walking. The ActivPAL is sealed in a waterproof sleeve and attached to the skin using hypoallergenic tape. Participants will be instructed to wear the ActivPAL for eight consecutive days. The first 24 hours of the data will be removed in order to counteract a possible Hawthorne effect.^29^ A valid day requires at least 10 hours of waking wearing time. Participants having at least three valid measurement days per time point will be used in the analysis.

**Tertiary outcomes** will be physical functioning (Short Performance Physical Battery^30^) at T0 and T1, sleep quantity and quality (Emfit QS sleep tracker^31^ and Pittsburgh Sleep Quality Index^32^ at T0, T1, T2 and T4), level of fatigue (Fatigue Severity Scale-7^33^ and Visual Analogue Scale at T0, T1, T2 and T4), self-efficacy (Self-Efficacy for Symptom Management Scale^34^ at T0, T1, T2 and T4), self-management skills (Patient Activation Measure^28^ at T0, T1, T2 and T4), end-user satisfaction (End-User Computing Satisfaction^35^ at T1), feasibility (Post-Study System Usability Scale^36^ at T1) and acceptability (System Usability Scale^37^ at T1) of the RISE eCoaching system and compliance to the treatment protocol. Compliance to the treatment protocol will be measured at T1 in the experimental group via a compliance questionnaire: (1) the number of people that completed the intervention (with and without missing sessions); (2) the number of participants that missed one or more of the face-to-face sessions, the reasons for missing and the percentage of missed sessions per participant; (3) the amount of sessions the PS was present; (4) the average amount of times participants used the app during the day.

Other outcomes will be stroke impact (Stroke Impact Scale – Physical^38^ at T0 and T1), mental health (Hospital Anxiety and Depression Scale^39^ at T0, T1, T2 and T4), comorbidities (Cumulative Illness Rating Scale^40^ at T0), Body Mass Index (at T0 and T1), walking speed (5-Metre Walking Test^41^ at T0 and T1), blood pressure, cognitive functioning (Montreal Cognitive Assessment at T0), patient characteristics (age, gender, education level, living situation (number of persons in the household) via intake questionnaire at T0), stroke characteristics (type of stroke, side of stroke, time since stroke via intake questionnaire at T0) and vascular risk factors (coronary artery disease, atrial fibrillation, diabetes, hypertension, clinical obesity, smoking and alcohol use, hyperlipidaemia via intake questionnaire at T0) and stroke severity (National of Health Stroke Scale^42^ at T0). All measurement instruments and accompanied time points are given in table 3.

### Sample size

The required number of subjects was calculated using the Lachin and Foulkes Logrank Test module in the PASS 2008 software (Hintze J. PASS 2008, Kayesville, Utah, USA www.ncss.com). The power calculation was performed based on detecting a difference in MACE between the experimental and control group. In line with the effectiveness of cardiac rehabilitation, we expect that the RISE intervention will decrease the number of MACE by 35%.^43^ In the control group, 25% is expected to have MACE in the first year.^3 44^ To not underpower the study, an event rate of 20% in the control group in the first year is used. Participants will enter the study during an accrual period of 1.5 years. Enrolment is assumed to be completed for 50% when 50% of the accrual time has passed. A follow-up period of 1 year is assumed to have a 20% loss to follow from the experimental group and a 20% loss to follow from the control group. A two-sided log rank test with a power of 0.85 and a 0.05 significance level to detect a difference of 0.07 between 0.80 and 0.87 (the proportions surviving the experimental and control group after 1 year) led to an overall sample size of 752 participants (of which 376 are in the experimental group and 376 in the control group).

*Sedentary prolongers* and *sedentary movers* will be the target population of the study and will be randomised to the intervention or control group. From our RISE cohort study, we know that 67% of the participants with stroke were *sedentary prolongers* or *sedentary movers*.^11^ Therefore, we expect around 1000 participants need to be screened during baseline measurement (figure 1). Based on our pilot study, we expect to include 2–3 participants per hospital per month. With 20 participating hospitals, this will lead to the expected number of 762 participants by December 2025.

Our secondary outcome, effectiveness of the RISE intervention on reducing SB, can be assessed in a smaller population. From the RISE pilot study, we know that the target group had an average of 11 hours and 21 min of sedentary time per day, with an SD of 77 min/day.^14^ This means, with a two-sided significance level of 0.05, a power of 80%, that a sample size of 47 people per group is needed to detect a minimal detectable change of 45 min in SB between our groups.^45^ Accounting for a dropout rate of 20%, 59 participants per group will be used for this analysis.

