**Methods and analysis:**

This assessor-blinded multicentre randomised controlled trial includes about 1000 participants with a first-ever stroke, of which 752 participants require secondary prevention based on their 24-hour movement behaviour. Participants will be randomly assigned to the experimental group (RISE intervention + usual care) or control (usual care) group. RISE is a 15-week blended care intervention: primary care physiotherapists coach people in their home setting using behaviour change techniques and the RISE eCoaching system. This system consists of: (1) an activity monitor, (2) a smartphone application that provides real-time feedback and contains e-learning modules and (3) a monitoring dashboard for the physiotherapist. A close relative of the participant is involved during the intervention to provide social support. The primary outcome is the effectiveness of the RISE intervention regarding the prevention of MACE measured at one year post randomisation using survival analysis comparing the experimental and control groups. Secondary outcomes include cost-effectiveness for MACE prevention and QALYs and changes in 24-hour movement behaviour over time using compositional data analysis.

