**Figure 1 F1:**
[figure not shown]
Flowchart of the RISE trial. Until one year post randomisation, occurrence of MACE, cost-effectiveness and 24-hour movement behaviour will be measured. All activities with the icon of a house will take place at the participants’ home.

**Table 1 T1:** Trial registration data

Data category	Information
Primary registry and trial identifying number	ClinicalTrials.govNCT06124248
Date of registration in primary registry	08 November 2023 earliest version24 September 2024 last update posted
Secondary identifying numbers	NL83940.000.23 (Medical Ethics Review Committee Utrecht NedMec)
Source(s) of monetary or material support	This work is supported by Dutch Research Council (NWO), Nationaal Regieorgaan Praktijkgericht Onderzoek SIA grant number RAAK-PRO04.093 and Care Research Netherlands & Medical Sciences ZonMW grant number 0930012310010.
Primary sponsor	University Medical Centre Utrecht
Secondary sponsor(s)	N.A.
Contact for public queries	[contact]
Contact for scientific queries	[contact]
Public title	RISE intervention: heading to sustainable movement behavioural change in people with stroke
Scientific title	Secondary prevention by striking the balance in 24-hour movement behaviour by empowering people at risk with a stroke: rationale and design of the RISE intervention randomised controlled trial
Countries of recruitment	The Netherlands
Health condition(s) or problem(s) studied	Stroke
Intervention(s)	Experimental group: RISE intervention and usual care. The RISE intervention is a 15-week blended care intervention: primary care physiotherapists coach people in their home setting using behaviour change techniques and the RISE eCoaching system. This system consists of: (1) an activity monitor, (2) a smartphone application that provides real-time feedback and contains e-learning modules and (3) a monitoring dashboard for the physiotherapist. A close relative from the participant is involved during the intervention to provide social support.
	Control group: usual care
Key inclusion and exclusion criteria	Ages eligible for study: ≥18 years. Sexes eligible for study: both.Accepts healthy volunteers: no

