### Study procedures

After obtaining informed consent (online supplemental file 1), baseline measurement (T0) takes place at the participants’ home (figure 1). During this visit, an activity monitor will be provided to objectify the 24-hour movement behaviour. If participants require secondary prevention, it will be based on their 24-hour movement behaviour pattern^11^: *sedentary prolongers,* ≥9.5 hours of sedentary time per day, >50% of the sedentary time is spent in bouts >30 min and not reaching the physical activity guideline (150 min MVPA during the week); *sedentary movers,* <9.5 hours of sedentary time and (1) ≤50% of the sedentary time spent in bouts >30 min or (2) not reaching the physical activity guideline.^16 17^ Randomisation will take place for *sedentary prolongers* and *sedentary movers,* with stratification according to these two profiles. All other participants will be excluded after baseline measurement.

Concealment of allocation will be ensured by individual randomisation by an independent researcher. Randomisation to either the experimental or control group will be done using a computer-generated random sequence with block sizes of two, four and six (Castor Electronic Data Capture 2021, Ciwit B.V., Amsterdam, The Netherlands).

The experimental group receives the RISE intervention from a trained primary care physiotherapist for 15 weeks. Follow-up measurements take place at the end of the intervention period (T1) (ie, 4 months post randomisation) and at 6 months (T2), 9 months (T3) and 12 months post randomisation (T4) (figure 1). Due to the nature of the intervention, participants and primary care physiotherapists will not be blinded for treatment allocation. The researcher who performs the measurements at T1 is blinded to treatment allocation.

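### The 752 participants at 85% power match a calculation that credits 1 to 2.5 years at risk; with MACE observed for at most 12 months each, power is about 69% to 73% on the plan's own planning inputs

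*Protocol article*

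**What the plan says.** Under Sample size, the protocol article says that the number was "calculated using the Lachin and Foulkes Logrank Test module in the PASS 2008 software". The inputs are:

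- control arm: "an event rate of 20% in the control group in the first year is used", set below the 25% that the investigators expect;
- effect: "to detect a difference of 0.07 between 0.80 and 0.87", in line with a 35% reduction;
- entry: "Participants will enter the study during an accrual period of 1.5 years", with half enrolled at half of that time, i.e. uniform entry;
- a 1-year follow-up period with 20% loss in each arm;
- "A two-sided log rank test with a power of 0.85 and a 0.05 significance level", leading to 752 participants, 376 per arm.

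On observation time, the Figure 1 legend says: "Until one year post randomisation, occurrence of MACE, cost-effectiveness and 24-hour movement behaviour will be measured". Study procedures and Table 3 make T4, at 12 months after randomisation, the last measurement. The abstract describes the primary outcome as "prevention of MACE measured at one year post randomisation using survival analysis", and the registration data in Table 1 give the same time point.

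**The concern.** In the Lachin-Foulkes set-up, the accrual period matters because follow-up runs to a common calendar end: someone who enters early is watched for longer than someone who enters late. With 1.5 years of accrual and 1 further year, potential observation runs from 1 to 2.5 years, with a mean of 1.75. A design that stops counting MACE at 12 months for everyone gains nothing from the length of accrual.

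If the calculation used the first model and the trial runs on the second, the primary analysis will have about one third fewer events than the 85% relies on. A null result would then be read as coming from a better-powered trial than it is.

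**Working it through.** **Inputs** (all from Sample size, except the 12-month cap)

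- Event hazards: control −ln 0.80 = 0.2231; experimental −ln 0.87 = 0.1393. Difference 0.0839, mean 0.1812, hazard ratio 0.624.
- Loss hazard: −ln 0.80 = 0.2231 per year in each arm (20% in a year, exponential).
- z(0.975) = 1.960; z(0.85) = 1.036; 1:1 allocation.

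**Formula**

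√N × |λ1 − λ2| = 1.960 × √(4f(λ̄)) + 1.036 × √(2f(λ1) + 2f(λ2)), where f(λ) = λ² / P(event).

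**1. Reproducing 752: uniform accrual over 1.5 years, study ends at 2.5 years**

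- P(event) is 0.2667 (control), 0.1780 (experimental) and 0.2239 (at the mean hazard), so f is 0.1867, 0.1090 and 0.1467.
- N = [(1.960 × 0.766 + 1.036 × 0.769) / 0.0839]² = 750.6, i.e. 376 per arm, 752 in total.
- Power at 752 is 85.1%. Expected events: 376 × (0.2667 + 0.1780) = 167.

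**2. Same inputs, observation capped at 12 months, 20% loss**

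- P(event) is 0.1800, 0.1168 and 0.1490, so f is 0.2766, 0.1660 and 0.2203.
- Expected events: 376 × (0.1800 + 0.1168) = 112.
- z = (√752 × 0.0839 − 1.960 × 0.9387) / 0.9409 = (2.300 − 1.840) / 0.9409 = 0.489, so power is 68.8%. A log-rank simulation with 4,000 runs gives 68.1%.
- For 85% power, N = 1,126.

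**3. Capped at 12 months, no loss**

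- P(event) is 0.20, 0.13 and 0.1657. Expected events: 376 × 0.33 = 124.
- z = (2.300 − 1.745) / 0.8924 = 0.622, so power is 73.3%. For 85% power, N = 1,013.

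**4. Do other 12-month calculations give 752?** At two-sided 0.05 and 85% power, without loss, Schoenfeld needs about 982, Freedman about 1,018 and two proportions 1,008 (1,064 with continuity correction). Dividing by 0.8 for loss gives about 1,227 to 1,330. One-sided 0.05 gives 806 to 1,023. Ending the study at the close of the 1.5-year accrual gives 1,497. Of the variants tried on the stated inputs, only the one in step 1 gives 752.

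**5. Expected control rate** (25% v 25% × 0.65 = 16.25%, 752 participants, 12 months): power is 80.2% with 20% loss and 84.2% with none.

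**6. Detectable hazard ratio** at 752, 85% power and a 20% control rate, 12 months, solving the same formula for the experimental hazard: 0.55 with 20% loss, 0.57 with none. The planned value is 0.624.

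**The case against.** Four points deserve weight.

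- **The 1 to 2.5 years is not written down.** The article speaks of a 1-year follow-up period. A reader might infer that the protocol itself promises longer observation; it does not. The inference rests on the named module, the accrual inputs and the exact match to 752. If 752 had instead been meant for 12 months each, it would be an arithmetic error with the same shortfall.
- **69% is conditional.** A reader might conclude that the trial's true power is 69%. The documents do not support that: the 20% control rate was a deliberately cautious choice, and at the expected 25% the power is 80% to 84%. This narrows the claim without removing it, since each of these figures is below 85%.
- **Loss may be smaller for this endpoint.** Under Primary outcome, MACE comes mainly from the general practitioner's record, so a missed visit need not censor a participant. The no-loss figure of 73% may be the nearer one under the planning inputs. This stands, although the article does not say what happens to record access after withdrawal.
- **Longer follow-up is not simply a repair.** A reader might infer that the sponsor must follow participants beyond 12 months. That would change the registered 1-year primary outcome and would assume that the effect persists well after a 15-week intervention, which nothing in the article shows. Nor would it restore the modelled case exactly: the article's recruitment window, November 2023 to December 2025, is longer than 1.5 years.

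Nothing in the article describes a common closing date for MACE follow-up that would reconcile the two designs.

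**Conclusion.** The stated 85% power does not belong to the design described. It matches a staggered-entry model with about 167 events, whereas the 12-month design yields about 112 to 124 under the planning inputs, with power of about 69% (20% loss) to 73% (no loss). With the expected 25% control rate and a 35% reduction the range is about 80% to 84%. These figures assume exponential event and loss times, proportional hazards and 752 randomised participants. The shortfall against 85% holds in all four scenarios; its size depends on the control rate and on how complete the record-based follow-up is.

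**What to change.** In Sample size, replace the 85% statement with figures for at most 12 months of observation per participant:

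- power at 752 of about 69% with 20% loss and 73% with none (20% v 13%), and about 80% and 84% at the expected 25% control rate;
- expected events of about 112 and 124 under the planning inputs;
- detectable hazard ratio at 85% power of about 0.55 with 20% loss and 0.57 with none, at a 20% control rate, in place of 0.62.

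This is a change of wording; its only downside is a less favourable stated figure. Collecting MACE from the general practitioner's record beyond 12 months is at most an option for the sponsor to consider, for the reasons given above, and the correction does not depend on it.
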